### **4.3 Study Exit or Termination**

#### **4.3.1 Criteria for Study Withdrawal**

Subjects may withdraw from the trial at any time on their own, or be withdrawn by the Investigator for safety or behavioral reasons, or because they are unable to comply with protocol-required study visit times or procedures at their site.

Reasons for withdrawal from the study may include:

1. Subject withdraws consent;

Note: Withdrawal of consent by default means that the patient can no longer be followed; the subject may also choose to discontinue study treatment.

2. The situation that the investigator considers necessary to withdraw from the study;
3. Lost to follow-up;
4. The subject died.

#### **4.3.2 Criteria for Discontinuation of Study Treatment**

Discontinuation of trial treatment does not constitute withdrawal from the study. Subjects who discontinue trial treatment must continue to complete the remaining visits as required by the protocol. The study treatment must be discontinued if the subject meets any of the following criteria:

1. The subject requests to discontinue the investigational drug;
2. The efficacy evaluation meets the criteria for disease progression confirmed by the investigator (according to RECIST 1.1 criteria);
3. The subject experiences a pregnancy event during the course of the study;
4. The subject is still unable to tolerate the toxicity after dose adjustment, or develops adverse events, laboratory abnormalities or concurrent diseases,

etc., and continues to participate in the study is not in the best interest of the subject as judged by the investigator;

5. Worsening of clinical symptoms (e.g. ECOG score  $\geq 2$  Or  $\geq$  Grade 2 dyspnea caused by persistent increased pleural effusion, etc.), making it impossible to continue the trial;
6. Significant protocol deviations such as subject ineligibility are found after enrollment;
7. Subjects who, in the opinion of the investigator, are noncompliant with study procedures or study drug administration should consult with the sponsor for instruction on handling the subject;
8. Other reasons that, in the opinion of the investigator, make continuation of study treatment impossible.

#### **4.3.3 Discontinuation from Study or Study Treatment of Steps**

If a subject was withdrawn from the study or discontinued study treatment, the following actions were taken:

1. The reason (s) must be documented in the medical file and eCRF;
2. An End of Treatment (EOT) visit should be performed. Tests done during the window before treatment withdrawal do not need to be done at the EOT visit. Inspections completed above, refer to the trial visit schedule;
3. The subject should be followed for safety for 30 days after the EOT visit or the subject starts a new anticancer therapy;
4. Subjects without disease progression should continue to undergo imaging evaluation at the scheduled frequency and time until the patient starts new anti-tumor treatment or disease progression. Every effort should be made to obtain imaging evidence of disease progression in such subjects;

#### **4.4 Lost to Follow-Up**

If a subject fails to return for a scheduled visit and the site staff is unable to contact him/her for at least 3 times, he/she will be considered lost to follow-up.

Contact information includes telephone, fax, SMS, social media tools and mail,

etc. All such attempts to contact the patient should be documented in the subject's medical record or in the study file. If it is determined that a subject has died, the study site will make every effort to obtain death information and cause of death, such as using public resources, such as community health registries and databases. If the subject's status is not available despite all attempts, the investigator should report the date the subject was last known to be alive and record in the subject's medical history.

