### 6.2.6 Follow-up Visit

After the end of treatment visit, enter the follow-up period. The safety follow-up period is the interval between the EOT visit and the scheduled follow-up visit, which should occur 30 days ( $\pm 7$  days) after the EOT visit or 30 days ( $\pm 7$  days) after study drug administration if the EOT visit was not performed. Adverse events and SAEs must be reported to at least 30 days after initiation of study drug, the date of the follow-up visit, or until the toxicities resolve, return to baseline, or are deemed irreversible, whichever is longer. Reasonable efforts should be made to have the subject return for the follow-up visit and report all AEs that occur during this period.

If a subject is scheduled to start a new antineoplastic therapy before the end of the safety follow-up period, the safety follow-up visit should be performed before the start of the new antineoplastic therapy. Once new antineoplastic therapy was initiated, subjects entered the survival follow-up period.

After completion of the safety follow-up period, enter into the survival follow-up

period. The first survival follow-up period (including telephone follow-up) occurred 8 weeks ( $\pm 7$  days) after the last safety follow-up and occurred on an 8-week ( $\pm 7$  days) basis until the subject died, lost to follow-up, the study was terminated by the sponsor, or other study closure criteria were met, whichever occurred first. The investigator may follow up the subject, his/her family or the responsible physician by phone to collect whether other anti-tumor treatment was given to the subject before this visit. If other treatments are used, the treatment regimen and cycle number and outcome must be recorded. The patients were followed up until death, and the relevant cause of death and specific time were recorded to obtain overall survival (OS).

For subjects who discontinue study treatment due to intolerance or other reasons, if no radiographic progression is observed, radiographic assessment should still be performed at the original frequency until disease progression or initiation of other anti-tumor therapy (except anti-tumor therapy with traditional Chinese medicine), and radiographic evidence of disease progression should be obtained as much as possible for such subjects.

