In this study, we preliminarily investigated the therapeutic effect of TQB2858 injection in advanced high-grade sarcoma and assessed the efficacy according to RECIST 1.1 evaluation criteria and iRECIST evaluation criteria. Indicators include objective response rate (ORR), disease control rate (DCR), progression-free survival (PFS), 3-month ORR, overall survival (OS) and duration of response (DOR).

- 1) Objective response rate (ORR): is the proportion of subjects whose tumor volume reduction reaches the prespecified value and maintains the minimum time limit (at the next imaging assessment), including cases of complete response (CR) and partial response (PR);
- 2) Disease control rate (DCR): the proportion of patients whose tumors shrink or remain stable for a certain period of time, including patients with CR, PR and stable disease (SD);
- 3) Progression-free survival (PFS): The time from the first dose to disease progression (PD) or death before PD; if there is no PD or death before PD, the date of the last imaging assessment will be used as the cut-off date;
- 4) Overall survival (OS): The time from the first treatment of a patient to death from any cause.
- 5) DOR: In subjects with CR or PR, the time from the first tumor assessment of CR or PR to PD or death before PD; if a subject with CR or PR did not experience PD or death before PD, the date of the last radiographic assessment will be used as the cut-off date.

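### Section 4.4 ties the public-record search to deaths already determined and does not require it when vital status is unknown, so Kaplan-Meier OS is at risk of being overstated if loss is linked to dying

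*Protocol*

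**What the plan says.** Section 4.4 classes a subject as lost when the subject "fails to return for a scheduled visit and the site staff is unable to contact him/her for at least 3 times". It lists telephone, fax, SMS, social media and mail as means of contact and asks that attempts be documented. It sets no interval between attempts.

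Section 4.4 then treats two situations differently:

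- **Death determined:** "If it is determined that a subject has died, the study site will make every effort to obtain death information and cause of death". Health registries and databases in the public domain are given as examples of where to look.
- **Status unknown:** "If the subject's status is not available despite all attempts, the investigator should report the date the subject was last known to be alive".

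Section 4.3.1 gives "Lost to follow-up" as a reason for withdrawal from the study. Section 6.2.6 runs the 8-weekly survival contacts "until the subject died, lost to follow-up, the study was terminated by the sponsor", or until other closure criteria are met. Note 4 to the visit schedule says the same. Section 6.2.6 also lets the investigator telephone the family or the responsible physician, and it speaks of following patients until death.

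Section 8 defines OS as running from first treatment to death from any cause. For PFS, "if there is no PD or death before PD, the date of the last imaging assessment will be used as the cut-off date". Section 11.3.7 estimates both by Kaplan-Meier.

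**The concern.** The record search is attached to the subjects for whom it adds least, those whose death is already established. It is not required for those in whom it could reveal a death. The threshold for loss is low: three calls on one day after a single missed visit would meet it, although survival contacts are 8 weeks apart. Once the threshold is met, the 8-weekly contacts stop.

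Kaplan-Meier assumes that a censored subject has the same prospects as those still at risk. In advanced sarcoma it is plausible that some subjects stop answering because they are deteriorating or have died. Those deaths would then be censored at the date last known alive, and OS would read too long. The trial has a single arm, so no control group carries the same error. Vital status is a matter of data collection: if it is never sought, no later analysis rule can restore it.

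**Working it through.** The protocol states no expected loss rate and no OS target, so there is no figure to reproduce. Two checks apply: what the text requires, and how large the effect could be.

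**1. What the text requires**

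| Situation of the subject | Record search required? | 8-weekly survival contact continues? |
|---|---|---|
| Reachable, alive | Not needed | Yes (6.2.6, note 4) |
| Death determined | Yes (4.4) | Not applicable |
| Unreachable, status unknown | Not stated; date last known alive (4.4) | No, ends at loss (6.2.6, note 4) |

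The gap is the third row.

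**2. Size of the effect on OS**

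Inputs:

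- Median OS of 49 weeks, from the soft tissue sarcoma cohort of the pembrolizumab trial described in section 1.1. It is used only as an illustration.
- Exponential survival and follow-up uniform between 52 and 104 weeks (assumed).
- A share q of deaths never learned of, each censored 0 to 8 weeks before death (assumed: 5%, 10%, 20%).

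If a share q of deaths is censored close to the time of death, the apparent hazard falls by the factor (1 − q). The apparent median is therefore about 49/(1 − q):

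- q = 5%: 49/0.95 = 51.6 weeks
- q = 10%: 49/0.90 = 54.4 weeks
- q = 20%: 49/0.80 = 61.25 weeks

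Simulation with 400,000 subjects under these assumptions:

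| Share of deaths missed | Linked to death: KM median | Loss independent of death: KM median |
|---|---|---|
| 0 | 48.9 weeks | – |
| 5% | 51.3 weeks | 48.9 weeks |
| 10% | 54.0 weeks | 48.9 weeks |
| 20% | 60.4 weeks | 48.9 weeks |

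In the last column, loss is an independent process that would remove the same percentage of subjects by week 52.

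A simulation at n = 100 (3,000 runs, 1-year uniform accrual, cut at week 104) gave medians of 48.5, 51.0, 54.1 and 60.8 weeks. One-year OS was 48.0%, 49.6%, 51.3% and 55.2%.

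**3. Small cohorts**

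Section 11.2 allows cohorts of 10. Under the same assumptions, λ = ln 2/49 = 0.01415 per week. The mean probability of surviving to the cut is (e^(−52λ) − e^(−104λ))/(52λ) = (0.479 − 0.230)/0.736 = 0.34. About 6.6 of 10 subjects would have died, so one missed death is 1/6.6, or about 15% of that cohort's deaths.

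**4. Size of the effect on PFS**

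A missed death matters for PFS only when it comes before progression. Take the 18-week median PFS from the same cohort, a share d of PFS events that are such deaths (assumed 10-20%) and q of those missed. The apparent median is 18/(1 − dq):

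- d = 10%, q = 5%: 18/0.995 = 18.1 weeks
- d = 20%, q = 20%: 18/0.96 = 18.75 weeks

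The shift is under one week.

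**The case against.** **Record searches may already be covered.** The sentence on unknown status refers to all attempts having failed, and a reader could take that to include the registries named just before. The document also reads as a rough translation. But the only attempts section 4.4 describes are contacts with the patient, and the registry wording hangs on a determined death. At best the text is ambiguous, which itself calls for a clearer sentence. It does not show that a search is forbidden.

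**Family or physician can be telephoned.** This is a real safeguard and a direct route to learning of a death. But it is optional, its stated purpose is to learn of other anti-tumour treatment, and it sits within the survival follow-up that ends at loss.

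**Loss need not be permanent.** A reader might infer that a lost subject is gone for good. The document does not say so. Three contacts is a minimum, nothing bars later contact, and section 4.3.1 says only of withdrawn consent that the patient can no longer be followed. What stands is that no route back is stated.

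**Bias is not shown.** This is correct. A reader might infer that OS will be overstated, but that requires loss linked to dying. The calculation assumes that link and shows no shift without it. Even at n = 100, the 95% margin on a one-year OS of 48% is about 1.96 × √(0.48 × 0.52/100) = 9.8 points, larger than the shift of 1.6 to 3.3 points at 5-10% of deaths missed.

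**Operational detail belongs elsewhere.** The spacing of calls may fairly sit in site procedures or the data management plan. Whether vital status is sought at all after loss is fixed by 4.4, 6.2.6 and note 4, and should be corrected there.

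**Conclusion.** The point holds as a gap in ascertaining vital status. As worded, section 4.4 requires no record search for subjects of unknown status, while note 4 and section 6.2.6 end survival follow-up for those subjects. If loss is linked to dying, OS is at risk of being overstated. From an assumed 49-week median, 5%, 10% or 20% of deaths missed would give about 51, 54 or 60-61 weeks. The fractions, the exponential form and the follow-up window are assumptions, and none comes from the protocol.

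A reader might extend the concern equally to PFS and DOR. That is not supported. Only deaths before progression matter there, the illustrative shift in PFS is under a week, and a record search recovers no missed scan.

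ORR is the primary endpoint (2.4), OS is secondary (2.5) and section 11.3.2 plans no hypothesis test. The priority is minor to moderate.

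**What to change.** - **Section 4.4:** require the public-record check, with family or physician contact, for every subject whose vital status is unknown. Do this before classing the subject as lost and again at data cut-off. Count any death found as an OS event.
- **Note 4 and section 6.2.6:** let loss to follow-up end visits but not vital-status checks, and allow reinstatement if status is later learned.
- **Reporting:** give the number of subjects with unknown vital status at data cut-off.

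Deaths found by record search should not be counted automatically as PFS or DOR events. A subject censored at the last scan could otherwise be credited with progression-free time up to a much later death, although progression may have gone unseen.

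The cost is protocol wording plus a few record checks and calls per lost subject, using sources the protocol already names. It needs no extra patients or procedures. OS may come out less favourable.

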#### **4.5 Exclusion criteria**

Subjects will be excluded if they meet any of the following criteria:

- 1) Patients who do not meet the inclusion and exclusion criteria are included in this study by mistake;
- 2) Wrong dose and method of administration;
- 3) Use of other chemotherapy, surgical treatment or investigational drug other than those specified in this protocol during the trial;
- 4) A serious deviation or violation of the protocol that affects the evaluation of the safety or efficacy of the investigational product.

The final eliminated cases shall be subject to the division decision of statistical analysis data set.

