## **11. Statistical Analysis**

## 11.1 Analysis Populations

Full Analysis Set (FAS): All the subjects who were enrolled and took the study drug at least once were included in the FAS. The following situations may lead to the exclusion of the enrolled subjects from the FAS: they did not meet the main criteria; they did not take the study drug once; they did not have any data after enrollment. Full analysis set is used for analysis of baseline and demographic data;

Safety Analysis Set (SS): all subjects who used the study drug at least once and had safety evaluation data; the safety population will be used for the analysis of safety data.

Effective Analysis Set (EAS): all enrolled subjects who have received at least one dose of the study drug and have at least one efficacy evaluation indicator. The purpose of this data set is to analyze the efficacy indicators of subjects.

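### Section 4.5 excludes treated subjects for later therapy, dosing error or ineligibility, while section 11.1 keeps them in the efficacy and safety sets; the protocol does not say which prevails

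*Protocol*

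**What the plan says.** Protocol section 4.5 states as a requirement that a subject is excluded on any one of four grounds. Condition 1 is enrolment of someone who turns out to be ineligible. Condition 2 is a dosing error, in amount or in route. Condition 3 reads: "Use of other chemotherapy, surgical treatment or investigational drug other than those specified in this protocol during the trial". Condition 4 is any other major breach of the plan that bears on how safety or efficacy is judged.

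The section names no analysis set and sets no cut-off at progression or end of treatment. It closes: "The final eliminated cases shall be subject to the division decision of statistical analysis data set".

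Section 11.1 defines three sets. The EAS is "all enrolled subjects who have received at least one dose of the study drug and have at least one efficacy evaluation indicator". The SS is "all subjects who used the study drug at least once and had safety evaluation data". Neither definition mentions later therapy, dosing error or ineligibility. The FAS, used for baseline and demographic data, may lose subjects who fail the main criteria. A per-protocol set appears only in the abbreviation list. Section 11.3.7 bases efficacy on the EAS.

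Section 4.3.2 keeps subjects who stop treatment in the study: "Subjects who discontinue trial treatment must continue to complete the remaining visits as required by the protocol". Section 6.2.6 has the investigator contact the subject, family or physician during survival follow-up "to collect whether other anti-tumor treatment was given to the subject before this visit", and follows subjects to death.

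**The concern.** The two sections give different instructions about who counts in the primary analysis. Section 4.5 tells the reader to exclude; section 11.1 tells the reader to include. The closing line of 4.5 hands the matter to an analysis-set decision without saying what that decision must respect.

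Condition 3 is the one that matters most for efficacy, because it can depend on outcome. Subjects whose tumours progress are the ones most likely to move to other chemotherapy or another trial drug. Removing them shrinks the denominator while most responders stay. With one arm per cohort and no hypothesis test (section 11.3.2), the ORR estimate and its interval are the main result, so a shift in the denominator goes straight into the conclusion.

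Conditions 1, 2 and 4 bear on safety. A subject who received the drug in error or at a wrong dose was still exposed, and safety is the secondary objective.

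**Working it through.** **Step 1: is there a defined set in which 4.5 could act without harm?**
- Section 11.1 defines FAS, SS and EAS only.
- Section 11.3.3 asks for subjects excluded from each analysis population to be tabulated, with protocol deviations and reasons. Deviation-based removal from the existing sets is therefore contemplated.
- Section 10.5 places a data review meeting before database lock. If sets are settled there, response is already known, because the trial is open-label.
- The synopsis describes the ORR denominator both as evaluable subjects (undefined) and as all cases, which does not settle the question.

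**Step 2: can condition 3 reach therapy given after progression?**
- For: stopping treatment is not withdrawal (4.3.2); follow-up runs to death (6.2.6); the last row of the table in 5.5.4 runs from the start of other antineoplastic therapy to the end of the trial, so later therapy falls inside the trial.
- Against: an earlier row of that table speaks of a period after withdrawal from the trial; section 5.5.1 prohibits concurrent anticancer treatment, and condition 3 could be its matching deviation rule.
- Result: the wording allows both readings.

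**Step 3: size, if 4.5 were applied to the EAS.** The protocol gives no power or precision calculation to reproduce; only the sample-size sums can be checked: 10 + 10 + 10 = 30 and 30 + 30 + 40 = 100, as stated.

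Inputs: n = 40 (upper limit of Cohort 3) and x = 7 responders. The 7/40 is the soft-tissue sarcoma result for another drug in section 1.1, borrowed as an assumption. Non-responders: 40 − 7 = 33. The number eliminated, e, is assumed; the documents give no share.

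ORR after elimination = x / (n − e), with the exact binomial (Clopper-Pearson) 95% interval, the method the protocol names.

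| Non-responders removed | e | ORR | 95% CI |
|---|---|---|---|
| none (11.1 as written) | 0 | 7/40 = 17.5% | 7.3–32.8% |
| about 10% | 3 | 7/37 = 18.9% | 8.0–35.2% |
| about 25% | 8 | 7/32 = 21.9% | 9.3–40.0% |
| about 50% | 16 | 7/24 = 29.2% | 12.6–51.1% |
| about 75% | 25 | 7/15 = 46.7% | 21.3–73.4% |

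Smallest cohort, assumed 2/10 = 20.0% (2.5–55.6%): removing 4 of 8 non-responders gives 2/6 = 33.3% (4.3–77.7%).

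**Step 4: direction.** If a fraction q of non-responders and r of responders are removed, ORR becomes x(1 − r) / [x(1 − r) + (n − x)(1 − q)]. This exceeds x/n whenever q > r. The table sets r = 0. If one responder also left in the row with e = 16, the result would be 6/(6 + 17) = 6/23 = 26.1% rather than 29.2%. Upward bias is thus probable but depends on non-responders leaving more often.

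**The case against.** A reader might infer that the protocol, as it stands, drops progressors from the analysis, inflates efficacy and loses safety data. The documents do not support that as a settled consequence. Section 4.5 defers to the analysis-set decision, and the EAS and SS as written remove none of these subjects. If 11.1 governs, inflation is zero and no subject leaves the SS.

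The rest of the case against has weight too. The four conditions look like ordinary per-protocol exclusions, and assigning deviations to sets is commonly left to a SAP, which may exist. Condition 3 may mean only concurrent therapy on treatment. It names chemotherapy, surgery and investigational drugs, whereas section 6.1 lists radiotherapy and targeted therapy separately, so not every later switch is caught. Responders who have surgery or a dosing error would leave as well. An upward bias in OS might also be inferred, but it is not established: removing subjects fit enough for further therapy could lower OS. The trial seeks preliminary efficacy without a test, so no type I error is affected.

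These points limit the size and certainty of the harm. They do not remove the conflict. The point is not that a per-protocol set is missing, but that the protocol states a mandatory exclusion contrary to its own set definitions and leaves open which one yields. A later SAP would have to contradict one of the two sections.

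**Conclusion.** The point holds as an internal conflict with a conditional consequence. Sections 4.5 and 11.1 disagree on whether dosed subjects with later therapy, dosing errors, ineligibility or serious deviations stay in the analysis, and the closing line of 4.5 leaves outcome-dependent elimination possible.

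- If 11.1 prevails: no bias.
- If 4.5 is applied to the EAS and condition 3 is read literally: ORR and DCR would probably be inflated. In the illustration ORR moves from 17.5% to 18.9% with about 10% of non-responders removed and to 29.2% with about 50%. This assumes 7/40 and that only non-responders leave.
- If 4.5 is applied to the SS: exposed subjects can be lost from the safety data; the number cannot be estimated from the document.
- For OS, the direction is not established.

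**What to change.** Amend sections 4.5 and 11.1 together, before results are reviewed:

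1. State that the four conditions remove no dosed subject from the EAS or SS as defined in 11.1. They serve only to flag protocol deviations or to define a per-protocol set for sensitivity analysis.
2. State that anti-cancer therapy after progression, or after study treatment has stopped, is not a ground for elimination.
3. For ORR and DCR, count assessments up to the first new anti-cancer therapy and keep the subject in the denominator.

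The cost is wording only. Later therapy is already recorded under 6.2.6, and section 8 already continues imaging until new therapy starts for subjects who stop without progression. The reported ORR may be less favourable than one computed after eliminations.
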